### Interventions

*Criteria for discontinuing allocated interventions for a given trial participant*

If any patients in any of the allocated groups develop any complication (
*e.g.*, deep venous thrombosis), their participation will be discontinued in the study. The patients will then receive appropriate care and offered outpatient rehabilitation as needed. Study participants will be retained in the trial (unless they withdraw their consent) to enable follow-up data collection and to prevent missing data.

*Adherence and concomitant care*

During the first consultation, the importance of following the study guidelines and adhering to the allocated group will be highlighted. Exercise adherence will be recorded as a percentage of completed exercises during the first follow up (after the six-week intervention) for both groups. Exercise adherence will be taken into consideration when performing the pre-protocol analysis.

All enrolled patients will be encouraged to contact the principal investigator directly if experiencing problems related to their allocated group intervention. The principal investigator will then fill out a standardized form at these calls. Patients can use medicines and nutritional products as needed, prescribed by their physician. To avoid study-contamination, patients will be asked to adhere to the allocated rehabilitation intervention and not to seek alternative health-care services during the course of the study. Patients will be advised to contact their general practitioner or the principal investigator as needed.

The physiotherapy intervention will be given to Groups A and B for six weeks. The intervention will be provided for 60 minutes, five days each week. Both Group A and Group B will receive conventional treatment. Group A will receive mCIMT along with the conventional therapy, while Group B will receive the motor relearning program along with the conventional therapy. Treatment will be provided to both groups for six weeks.

*Modified constraint-induced movement therapy (mCIMT)*

Exercises will be given to participants that have a functional focus and will be under supervision. The affected lower extremity will be the focus of these exercises. Based on the desired movements, the therapist (principal investigator) recommended these exercises.

The 30-minute mCIMT approach will consist of the following movements: Transfer package (10 minutes per session), side stepping, ball kicking, stair climbing, and knee control on a step.

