### Sample size calculation

We estimated the sample size using a power analysis with 80% power and 5% Type 1 error for the main variables. The BBS score, in comparison to the difference in mean score pre and post treatment for mCIMT group from baseline to end visits. For the study, we used the previously determined effect size difference in percentage from the RCT.
^
22
^ Formula using mean difference:

$$n1=n2=2\frac{{\left(Z_{\alpha }+Z_{\beta }\right)}^{2}\sigma^{2}}{{\left(\delta \right)}^{2}}$$
Primary Variable (BBS)

Mean ± SD (Pre) result on BBS for mCIMT = 48.8 ± 4.7

Mean ± SD (Post) result on BBS for mCIMT = 52.5 ± 3.5

Difference = 3.7

Pooled std. dev. = (4.7 + 3.5)/2 = 4.1

$$\text{N1}=2^{*}\left[{\left(1.64+0.84\right)}^{2}{\left(4.1\right)}^{2}\right]/{\left(3.7\right)}^{2}=15$$

Considering 10% dropout = 2

Total samples required = 15 + 2 = 17 per group.

Total sample size required = 15

Notations:

$$Z_{\alpha }=\text{1.64 bat 5\% l.o.s. at both sides total 10\% type I error}$$

α=Type I error at 5%

$Z_{\beta }=0.84\;\left(1-\beta \right)=\text{Power at}\;80\%$

σ=std.dev=0.5pooledstd.dev

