### Data collection methods

Before group allocation, screening of the participants as per the inclusion and exclusion criteria will be carried out. This will be followed by baseline assessment of the outcome measures as mentioned. All participants will undergo the randomization process and are allocated into either group A or Group B. The intervention will be administered for an hour daily, five days per week for six weeks. The post intervention data for the outcomes will be recorded after the last intervention session day. The data will be compiled and analysed for studying the results. The study interventions will be administered by the principal investigator under the supervision of the guide throughout the duration of the study. The patients will be instructed and reminded of the sessions in advance through messages sent to their mobile phones so that adherence to the study is ensured. Furthermore, if the patient misses their sessions due to any reason, the standby days from the week will be utilized such that the patient receives a total of 30 sessions of intervention in the six week duration.

As per in the sample size calculation we have given a 10% dropout rate so that it does not interfere with the results of our study.

The data collection forms can be found as
*Extended data.*
^
24
^

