### Statistical analysis

Samples taken in accordance with the protocol and recorded on a basis that includes all relevant characteristics. Dataset of outcome variables including demographic, physical, laboratory and vitals information will be collected and tabulated in Excel, and will be analysed using R-Software version 4.3. Demographic variables such as age and gender and physical examination (height, weight, BMI), laboratory parameters (haemoglobin, Erythrocyte Sedimentation Rate (ESR), Liver Function Test (LFT), Kidney Function Test (KFT)), and vitals (respiratory rate, pulse rate, systolic blood pressure, diastolic blood pressure and SpO
_2_ levels) will be collected. Outcome variables such as BBS, DGI, TIS, 10MWT, FRT and FES will be presented over descriptive statistics with categorical tabulation for frequency and percentage, while quantitative measurements with minimum, maximum, mean and standard deviation.

The primary outcome variables will include the BBS for measuring balance and the DGI for measuring gait outcome variables, the secondary outcome variables include the TIS, FRT, 10MWT and FES. Variables as primary and secondary parameters for their measuring assessment at different time visits will be assessed to find the significance in mean at 5% level of significance at P-value < 0.05. Statistical analysis will be performed for hypothesis testing for paired pre and post analysis using a paired t-test for normal data or non-parametric test such as Wilcoxon signed-rank test for non-normal data. Similarly, an unpaired t-test will be used for two independent groups for the change in parameters readings of primary and secondary variables at two different visits.

Data over the outcome variables will be analysed for normality (normal distribution) using Kolmogorov–Smirnov test. If data results over non normal distribution then alternate non parametric test will be used.

Confounding variables will be analysed with generalised linear model to find the random and fixed effects over the outcome variables. Association analysis for finding significance of cofounding parameters will be examined by using Chi-squared test or Fisher’s exact test or by using multi-variant analysis.

Full analysis set for the values of outcome variables will be analysed for the results missing data will be covered with imputation method by calculating the mean and median over the existing data.

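### Missing outcomes are to be filled with an unspecified mean or median and then put through an ordinary t-test on change; no reading of this rule is reliably sound

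*Protocol article*

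**What the plan says.** Statistical analysis in the protocol article fixes three things. The analysis set: "Full analysis set for the values of outcome variables will be analysed". The handling of gaps: "missing data will be covered with imputation method by calculating the mean and median over the existing data". The group comparison: "an unpaired t-test will be used for two independent groups for the change in parameters readings of primary and secondary variables", judged at 5%, with a non-parametric alternative for non-normal data. No variance correction or missing-data sensitivity analysis goes with the imputation.

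Two other sections bear on the point. Data collection methods says of the sample size that "we have given a 10% dropout rate so that it does not interfere with the results of our study". Interventions, under the criteria for discontinuing allocated interventions, says of patients with a complication that "their participation will be discontinued in the study". Two sentences later it says: "Study participants will be retained in the trial (unless they withdraw their consent) to enable follow-up data collection and to prevent missing data".

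**The concern.** A value copied from the average of other patients carries no information about the patient it stands for. A plain t-test nevertheless counts it as a full observation. Depending on what is filled and from which patients, the test can overstate its precision or the arms can be pulled together. The sentence leaves three choices open (own arm or pooled, mean or median, score or change), so the analyst would choose among them, possibly after seeing the data.

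At stake are the primary comparisons of the Berg Balance Scale (BBS) and the Dynamic Gait Index in a 34-patient trial, where two filled values per arm are enough to move a p-value or an estimate. The dropout allowance does not remove the problem. Extra patients protect the numbers analysed, but they do not correct a bias from who is missing or from how the gaps are filled.

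**Working it through.** **Inputs.** From Sample size calculation: BBS 48.8 ± 4.7 before and 52.5 ± 3.5 after treatment, difference 3.7, SD 4.1, and 15 + 2 = 17 per group. The test is the unpaired t-test on change at 0.05, taken here as two-sided because the protocol does not state sidedness. Data are assumed normal and missing completely at random. The pre-post correlation is not given, so a range of 0.3 to 0.9 is assumed.

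**The plan's own figure.** 2 × (1.64 + 0.84)² × 4.1² / 3.7² = 15.1, stated as 15. Adding 2 for dropout gives 17. The planned case is therefore n = 17 per arm with k = 15 observed.

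**Reading 1: own-arm mean of the change.**
- The filled values add nothing to the sum of squares, so the expected sample variance is σ² × (k − 1)/(n − 1) = σ² × 14/16.
- The t-test divides this by 17, although only 15 values carry information.
- Reported SE / true SE = √(14/16 × 15/17) = 0.879, which is about 12% too small.
- With σ = 4.1, the true SE is 4.1 × √(2/15) = 1.50 and the reported SE is 1.50 × 0.879 = 1.32.
- The critical value on 32 degrees of freedom is 2.037. Multiplied by 0.879 it is 1.790, which on 28 degrees of freedom has a two-sided tail area of 8.4%.
- A simulation of 100,000 trials agrees (8.4% to 8.5%, mean or median). One missing per arm gives about 6.5%, and three give about 10.8%.

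**Reading 2: own-arm mean of the week-6 score, with change then taken from the patient's own baseline.** Filled changes now vary with the baseline, so the SE error is smaller and can go either way. With the SDs of 4.7 and 3.5 and 2 missing per arm, simulation gives:

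| Assumed correlation | Type I error |
|---|---|
| 0.3 | 6.0% |
| 0.5 | 5.7% |
| 0.7 | 5.2% |
| 0.8 | 4.8% |
| 0.9 | 4.1% |

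The ratio of reported to true SE runs from about 0.95 to about 1.04. It passes 1 because a filled change has the spread of the baseline (SD 4.7), whereas at a correlation of 0.9 a real change has SD √(4.7² + 3.5² − 2 × 0.9 × 4.7 × 3.5) = 2.17.

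**Reading 3: mean of both arms pooled.** Both arms receive the same filling value, so only the observed share of the difference survives: 3.7 × 15/17 = 3.26, a loss of 12%. With three missing per arm it is 3.7 × 14/17 = 3.05. Type I error stays at about 5.0%. When change is filled, power is 0.664, against 0.665 for observed cases.

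**Comparison: no filling, 15 against 15.** The mean difference is 3.70, true SE 1.49, reported SE 1.50, type I error 4.9% and power 0.665.

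**Complications.** The two Interventions sentences, set side by side, allow two outcomes. If leaving the study means no week-6 assessment, a patient with a complication receives an average taken from those who completed. If retention for follow-up governs, that patient has an observed score and nothing is filled. The figures above assume random missingness and contain none of the bias that the first case could add.

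**The case against.** The strongest counter-argument concerns size. A reader might infer that the rule raises the false-positive rate to 8.4%. That figure needs the change score to be what is filled, and the protocol does not say so. It speaks of values of outcome variables, so filling the week-6 score is at least as natural a reading, and there type I error stays within about 4% to 6%. With a correlation of 0.7 to 0.8, own-arm filling of the score does little harm under random missingness. This stands: 8.4% belongs to one reading and is not the result of the rule as such.

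Pooled filling leaves type I error near 5% and is conservative for a superiority claim. This also stands, but the reported effect is still biased.

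A reader might also infer that patients who stop because of complications will be credited with an average gain. The documents do not establish this. The passage is headed as criteria for stopping the allocated intervention and says that participants are retained for follow-up, so therapy may stop while assessment continues. The risk is conditional on which sentence governs.

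Data management expects high retention, and with complete follow-up the rule has no effect. Yet the sample size budgets for two losses per arm, and the rule exists for that case. Finally, the sentence on the 10% allowance can be read loosely as a remark about adequate numbers. Rewording it is then a clarification.

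None of this rescues the rule. It is a method the protocol itself states, so it cannot be set aside as detail left to an unseen analysis plan, and its soundness depends on choices and a correlation that the protocol does not give.

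**Conclusion.** The point holds as a should-fix. At the protocol's own allowance of 2 missing of 17 per arm, the consequence depends on the reading: an SE about 12% too small with type I error of about 8.4% (own-arm change), type I error of about 4% to 6% (own-arm week-6 score), or a 3.7-point difference reported as about 3.26 with type I error near 5% (pooled). These figures rest on normal data, a two-sided test, data missing completely at random and, for the second reading, an assumed correlation of 0.3 to 0.9. Missingness related to outcome could add bias under any reading, and the 10% allowance would not prevent it.

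A must-fix grade is not supported. The largest figure rests on one unstated reading, the harm linked to complications is conditional, and the effect vanishes with complete follow-up.

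**What to change.** 1. In Statistical analysis, delete the mean and median imputation. Suggested text: *The primary comparison uses observed week-6 outcomes of all randomised patients, analysed by assigned arm, without single imputation. As a sensitivity analysis, missing week-6 scores are multiply imputed using arm and baseline score.* The planned comparison on observed cases already restores about 5% type I error under random missingness. Adjusting for the baseline score, which is collected anyway, is an optional gain and not needed for this repair.
2. In Data collection methods, say that the 10% allowance preserves the number of patients analysed and makes no claim about bias.
3. In Interventions, reconcile the two sentences so that it is clear whether outcome assessment continues after the allocated therapy stops.

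The cost is a few lines of wording and slightly wider confidence intervals than own-arm filling of change would report. Protocol amendments says that further changes could not be made, but Study status says the trial has not begun, so a documented amendment before any data exist is the time to do this.

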### Monitoring

*Data monitoring*

We will have a data monitoring committee lead by the PI for maintaining and integrating of the data.

*Harms*

The whole procedure is going to held under the supervision of clinicians and departmental committee During the trial, harms and adverse event will be immediately reported to the committee. The final dataset will be uploaded to the institutional research website and will be accessible to concerned authorities.

*Auditing*

Every month, auditing of the trial is going to be conducted. Any deviation from the protocol will be documented and will be addressed.

## Ethics and dissemination

### Ethical considerations

Datta Meghe Institute of Higher Education and Research, Sawangi Wardha granted ethical approval (date, 21/03/2023) (reference number, DMIHER (DU)/IEC/2023/813). This protocol has been registered on CTRI (trial registration number,
CTRI/2023/05/052674; registration date, 16/05/2023).

### Protocol amendments

The study has been approved by the Scrutiny Committee at the college level on 01/03/2023 and by the IEC at the university level on 21/03/2023 following which, CTRI registration was also done. As per the suggestions through these committees the study has already been modified and approved. So further changes could not be carried out.

### Consent

Members of the trial committee will provide the consent form to the participants in the trial and will inform and explain all the potential benefits and risks to the participants.

### Confidentiality

The study program will be elaborated to the participant and one of their relatives, and the principal investigator will take personal information as a part of procedure. The consent form will include the confidentiality statement and signatures of the principal investigator, patient and two witnesses. Whenever it’s necessary to divulge details for the study, consent will be obtained from the patient with complete assurance of their confidentiality.

### Access to data

The Principal Investigator will have access to the final trial datasheet.

### Ancillary and post-trial care

The whole procedure is going to held under the supervision of clinicians and the departmental committee
*i.e.*, Guide, Head of department, Principal and member of Research Guidance Cell.

After the trial session, the participations are going to be under supervision for about four weeks so that if there will be any harm, the Principal Investigator will take care of the participants.

### Dissemination policy

We will present the work in International Conference Proceedings and publish in an indexed journal.

**Study status**

The study is yet to begin.

## Discussion

The study’s primary objective is to determine how well mCIMT and MRP work to treat balance and gait issues. These cause a rise in the risk of falling, which further reduces the functional independence of those who had sub-acute stroke. In a previous study, the experimental group received mCIMT for two weeks, while the control group received neurodevelopmental therapy (NDT). The findings showed that mCIMT for lower limb had a superior impact on improving motor function compared with NDT.
^
22
^ Using a randomized controlled trial, the study was done to determine how well the MRP worked to improve balance and upright mobility in sub-acute stroke patients. The results suggested that MRP showed a good impact on post-stroke survivors with the experimental group receiving MRP in addition to conventional physical therapy (RPT) for a duration of five days per week for eight weeks.
^
23
^ Both interventions were found to be beneficial in hemiplegic stroke when compared with a negative control group. But there is dearth of literature reflecting the superiority of either of these interventions when compared with each other. Therefore, our study will compare the two regimes to evaluate which is more successful while looking at the effectiveness of these therapies in sub-acute stroke patients.

## Data Availability

No data are associated with this article. Zenodo: Extended data - [name].docx,
https://doi.org/10.5281/zenodo.8172474.
^
24
^ This project contains the following extended data:
-Model consent form-Data collection form-Schedule of enrolment, interventions and assessments. Model consent form Data collection form Schedule of enrolment, interventions and assessments. Zenodo: SPIRIT- [name].docx,
https://doi.org/10.5281/zenodo.8172339.
^
25
^ Data are available under the terms of the
Creative Commons Attribution 4.0 International license (CC-BY 4.0).
